Q 76-93	Symptoms of burnout	Items from the Shirom-Melamed Burnout Questionnaire (SMBQ) [43]
Q 94	General health	One item from the SF-36 scale [44]

During the intervention, all participants in the intervention group were offered clinical advice by phone or e-mail from the specialist physicians at the Institute of Stress Medicine.

The control group started inclusion at the same day as the first training day for the intervention group, in November 2016. After providing their informed consent, patients at the control centers received TAU, which can include for example medical treatment, and psychological therapy. At some of the control centers, TAU also included RC getting in contact with employers, but normally this is done long into the sick-leave period.

Inclusion of patients lasted from November 2016 until the end of January 2018. The recruitment period was extended by six months compared to the original plan. During the intervention, the researchers revisited all centers for at least one occasion to encourage GPs and RCs to recruit patients. News letters from the project were regularly sent to all PHCC managers and RCs at both intervention and control centers. Also, research assistants contacted all RCs once a month by phone for follow-up.

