#### Sample size

In all 135 patients were recruited; 69 to the control group and 63 to the intervention group (see Fig. 1). Depending on the proportion of patients on sick-leave at three, six and twelve months after inclusion, power will vary between 41 % and 74 % (based on the assumption that the prevalence of sick-leave in the control group fluctuates between 20 % and 95 % and with an estimated difference between the groups of 15 % [45]; a two-sided test and a statistical significance of p < 0.05). There was a substantial variation in the number of recruited patients per PHCC.

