#### Outcome measurements and statistical analyses

The primary outcome of the RCT is RTW. We will analyze the difference between cases and controls in proportion of patients on full- or part-time sick leave at three, six and 12 months after inclusion. We will use data from the Swedish Social Insurance Agency’s Micro Database for Analyzing Social insurance (MiDAS) where all sick-leaves exceeding two weeks are registered. The intention to treat principle will be followed.

The intervention is designed to facilitate for the caregiver to involve the employer in rehabilitation and strengthen the patient’s RTW-SE, but whether these mechanisms are triggered or not will depend on circumstances among patients, employers as well as the caregivers, i.e it will depend on contextual factors [46]. For example, the effect of the intervention on RTW might depend on the patient’s symptom severity, the employer’s readiness for work adaptation, or on the caregivers’ adherence to the protocol. In order to conduct sub-group analysis within the intervention group, a follow-up questionnaire is sent to the patients’ home address by mail at six and 12 months after inclusion. In addition to questions about the rehabilitation process, the questionnaire contains the same items as the baseline measurement. For example we will explore how gender, age, occupation, symptom severity, employer activities and RTW motivation affect RTW.

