One reason why earlier studies within this field points to contradictory results [11, 49] might be that RCT studies commonly strive to reduce the variation between study participants and their contextual environment, instead of using these differences to explain how and why the intervention can have different effects on different groups of people. In the current study we instead assumed that implementation would depend on contextual factors at the organizational level, for example on the pre-existing routines, level of corporation and the total workload among GPs and RCs at each center. We also assumed that the impact of the intervention would depend on for example symptom severity and motivation to RTW among patients. The project design was based on these assumptions; numerous centers were recruited, matched and randomized, and patients in the intervention group were asked to reply to several questions at repeated occasions. However, the evaluation of how contextual and individual level factors effect RTW will also be constrained by the small sample size.

Preliminary analyses of the qualitative interviews conducted before and after intervention point to a set of organizational preconditions which need to be in place for GPs and RCs to be able to engage in a successful corporation. The strength of this study will be that the multitude of organizational level data can shed light upon facilitating and hindering factors for employer involvement in the primary care setting. There are many lessons to be learned about how primary care can face the challenging task of employer involvement: What motivates GPs to corporate with RCs? What do RCs need from their organizations to guide patients with stress-related disorders back to work? How can PHCCs ensure routines for sickness certification that enhance RTW? Such knowledge will be valuable for clinicians and policymakers in their future efforts to organize primary health care for improved RTW rates among patients with stress-related disorders. Results from the study will be communicated to the participating centers and other relevant stakeholders, and disseminated through scientific publication.

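### The sub-group analysis is set within the intervention group, so it can identify predictors of return to work but not for whom the intervention works

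*Protocol article*

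**What the plan says.** All references are to the protocol article.

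- **The question.** Outcome measurements and statistical analyses says that "the effect of the intervention on RTW might depend on" the patient's symptom severity, the employer's readiness to adapt work, or the caregivers' adherence. The Discussion faults earlier trials for reducing variation instead of "using these differences to explain how and why the intervention can have different effects on different groups of people", and says the project was designed on that basis.
- **The analysis.** The same Outcome section continues: "In order to conduct sub-group analysis within the intervention group, a follow-up questionnaire is sent to" patients at six and 12 months. The questionnaire repeats the baseline items. It then says: "For example we will explore how gender, age, occupation, symptom severity, employer activities and RTW motivation affect RTW".
- **Whose data.** The Discussion states that "patients in the intervention group were asked to reply to several questions at repeated occasions". The intervention section describes the baseline questionnaire, the employer form and the adherence checklist as parts of the four-step procedure. For the other arm it says: "After providing their informed consent, patients at the control centers received TAU". It describes no questionnaire for controls.

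The article describes no comparison of the two arms within levels of any factor.

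**The concern.** The question is about effect modification and the analysis is about prognosis. Among intervention patients alone, the association between a factor and RTW combines what the factor would have done under usual care with any change the intervention makes to that association. Only controls at the same level of the factor can separate the two.

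The problem is practical. The Background section itself counts symptom severity among the important individual-level variables for RTW. Patients with severe symptoms would therefore be expected to return later in either arm. If that pattern is seen among intervention patients and read as an answer to the stated question, it would suggest that the procedure works less well in severe cases, even if the benefit is the same at every severity. The design is presented as able to explain differing effects, so this part of the results is likely to be read that way.

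**Working it through.** **Inputs from the article (Sample size).** Arm sizes are "69 to the control group and 63 to the intervention group", which sum to 132. The power statement assumes that "the prevalence of sick-leave in the control group fluctuates between 20 % and 95" %, a difference of 15 points, and a two-sided 5 % level. The implied intervention-arm prevalence runs from 20 − 15 = 5 % to 95 − 15 = 80 %.

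**The article's own figure.** A two-proportion normal approximation with pooled variance, 69 against 63 and no clustering gives a minimum power of 40.5 % (57.5 % against 42.5 %), 74.0 % at 20 % against 5 %, and 75.0 % at 95 % against 80 %. The stated range of 41 % to 74 % is reproduced. It concerns the main comparison only.

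**Assumed for illustration.** A two-level factor split 50:50, so 34.5 controls and 31.5 intervention patients per level on average; the sick-leave rates below; no clustering. Power is Φ(|d|/SE − 1.96), plus a negligible opposite tail.

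*Case A: prognostic factor, no modification.* Controls 40 % and 70 % on sick leave, intervention 25 % and 55 %.
- Effect: 25 − 40 = −15 and 55 − 70 = −15 points, so the interaction is 0. The odds ratios are also close: (0.25/0.75)/(0.40/0.60) = 0.50 and (0.55/0.45)/(0.70/0.30) = 0.52.
- Within-arm contrast: 55 − 25 = 30 points. SE = √[(0.25·0.75 + 0.55·0.45)/31.5] = 0.1175. Power = Φ(0.30/0.1175 − 1.96) ≈ 72 %.
- A two-arm interaction test on the risk-difference scale rejects at its nominal 5 %.

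*Case B: true modifier.* Controls 40 % and 70 %, intervention 40 % and 40 %.
- Effect: 0 and −30 points, so the interaction is −30 points.
- Within-arm contrast: 0 points, significant 5 % of the time.
- Interaction test: SE = √[(0.40·0.60 + 0.70·0.30)/34.5 + (0.40·0.60 + 0.40·0.60)/31.5] = 0.168. Power = Φ(0.30/0.168 − 1.96) ≈ 43 %.

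The one-arm analysis tends to flag the factor that does not modify the effect and to miss the one that does.

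**How often, for a continuous factor.** Simulated logistic regression in 63 intervention patients, no true interaction, no clustering:
- Odds ratio 2.0 per SD: significant in about 12 %, 51 %, 68 % and 52 % of trials at sick-leave prevalences of 5 %, 20 %, 50 % and 80 %.
- Odds ratio 1.5 per SD: about 7 % to 35 % across the same prevalences.
- The allocation-by-factor test on 132 patients stays at or near 5 % or below.

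**What an interaction test can detect.** With 80 % power and average prevalence p, the smallest detectable interaction is 2.80·√[p(1−p)(2/34.5 + 2/31.5)]. This is 39 points at p = 20 % and 49 points at p = 50 %. For the main effect, 2.80·√[p(1−p)(1/69 + 1/63)] gives 20 and 24 points.

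**The case against.** **The analysis is exploratory, and limits are conceded.** The sentence on what will be explored can be read literally as a search for predictors, and the Discussion admits that the small sample constrains this work. That admission concerns precision. More patients in the same arm would not supply the missing comparator. The literal reading also does not answer the question posed just before it, nor serve the purpose given in the Discussion.

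**Details may be left to an analysis plan.** Details may be, but the article itself fixes the analysis population, and that population does not fit the question.

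**For several named factors no control contrast exists.** This stands. The employer form and the checklist arise from the intervention procedure, and severity and motivation come from a questionnaire not described for controls. For these factors the remedy is correct labelling, not a new test.

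**Stronger readings that the text does not support.**
- A reader might infer that six- and 12-month answers will be used to explain sick leave at the same or earlier times. The article does not say so. Baseline values exist, and the six-month questionnaire precedes the 12-month outcome. The text leaves the choice open.
- A reader might infer that an adherence comparison will mislead because early returners never reach the fourth step. This is plausible, but nothing in the article reports it. Adherence is named as a possible influence and is not in the list of factors to be explored.
- A reader might infer that unfounded moderator claims will be published. The article makes no such claim.

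**Conclusion.** The mismatch is real: the stated question needs both arms, and the stated analysis uses one. As written, the analysis can identify predictors of RTW among intervention patients and cannot establish effect modification in either direction.

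No single error rate can be given. The range of roughly 7 % to 68 % rests on an assumed odds ratio of 1.5 to 2.0 per SD, intervention-arm prevalences of 5 % to 80 %, and no clustering; the upper end needs the stronger association and a prevalence near 50 %. These figures are the power to find a genuine prognostic association. They become error rates only if the finding is called effect modification. Cases A and B also rest on assumed rates; they show the direction of the problem, not its expected size.

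The intention-to-treat comparison of sick-leave proportions is untouched. The point should be corrected because it changes what the trial can conclude about for whom the intervention works.

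**What to change.** 1. For baseline factors held in both arms, test allocation-by-factor interactions on all 132 patients, allowing for centre. Age and gender are candidates; occupation, F43 subcode and prior sick leave are others if held for controls. The article does not list what is held for controls, so confirm this first. Label the tests exploratory and low-powered.
2. For factors held only for intervention patients (symptom severity, RTW motivation, employer activities and readiness, adherence), report associations as predictors of RTW within that arm, and state that they do not show effect modification.
3. Use baseline values of questionnaire items. State that six- and 12-month answers will not be used to explain sick-leave status at the same or an earlier time.
4. Describe adherence at centre level within the process evaluation already planned. A complier-average estimate with allocation as instrument is not recommended: training and specialist advice could act outside the four steps, and some control centres also contacted employers.
5. Bring the Discussion's wording on explaining different effects into line with what these analyses can show.

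The cost is wording and a few extra models, with no new data collection. The downside is that fewer moderator claims can be made, since only interactions of about 39 to 49 points would be detected with 80 % power under the assumptions above.

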## Methods/Design

### Aim

The overall aim of this study is to evaluate whether a systematic procedure of cooperation between GPs and RCs which involves the employer can reduce the time for RTW in patients with stress-related disorders during a 12-month follow-up period. An intervention group will be compared to treatment as usual (TAU). The primary hypothesis is that an early contact between caregiver, patient and employer can stimulate the employer to take measures at the workplace that advance patients’ RTW. However, we expect this relationship to depend on various circumstances, both at the patient and the organizational level, such as the patient’s symptom severity and motivation to RTW, and the participant GPs’ and RCs’ possibilities to adhere to the intervention.

The second aim of the study is to investigate the organizational prerequisites for primary health care centers (PHCC) to involve the employer at an early stage of rehabilitation. This will be done by a process evaluation, using interviews and register data at the center level.

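### Whether the intervention's effect depends on patient factors is to be examined in the intervention arm alone, which shows who returns to work but not for whom the intervention changes it

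*Protocol article*

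**What the plan says.** The question is one of effect modification. Under Aim, after the primary hypothesis, the article says: "However, we expect this relationship to depend on various circumstances, both at the patient and the organizational level", and names symptom severity and motivation among them. Under Outcome measurements and statistical analyses it says that "the effect of the intervention on RTW might depend on the patient’s symptom severity", on the employer's readiness to adapt work, or on caregivers' adherence. The Discussion criticises earlier trials for reducing variation between participants rather than using it to "explain how and why the intervention can have different effects on different groups of people", and says the project design rests on that idea.

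The method is then stated: "In order to conduct sub-group analysis within the intervention group, a follow-up questionnaire is sent" by mail at six and 12 months, repeating the baseline items and adding questions on the rehabilitation process. The section closes: "For example we will explore how gender, age, occupation, symptom severity, employer activities and RTW motivation affect RTW". The Discussion confirms where the repeated data come from: "patients in the intervention group were asked to reply to several questions at repeated occasions".

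For control patients, the section on the intervention describes only consent and treatment as usual. No comparison of these factors across arms is described. The only limitation given for this part of the work is the small sample.

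**The concern.** An intervention effect is a contrast between arms, and effect modification is a difference between two such contrasts. A sub-group analysis in one arm contains neither. It estimates how RTW varies with a factor among treated patients, which combines the variation that would exist under usual care with any variation in the effect.

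The article's own Background lists symptom severity as a general determinant of RTW in common mental disorders. A gradient by severity is therefore to be expected in the intervention arm even if the procedure does nothing. Worded as a circumstance on which the effect depends, such a gradient would be a wrong answer to a question the article puts at the centre of its design. The reverse can also happen: a real difference in effect can be cancelled by prognosis and go unseen.

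**Working it through.** **Inputs from the article (Sample size).** 69 control and 63 intervention patients; two-sided test at 0.05; difference of 15 points; control sick-leave rate 20 % to 95 %; stated power 41 % to 74 %.

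**The plan's own figure.** Power = Φ[(0.15 − 1.96·SE₀)/SE₁], with SE₀ from the pooled rate and SE₁ from the separate rates.
- Control 20 %, intervention 5 %: pooled rate (13.8 + 3.15)/132 = 0.128; SE₀ = 0.0583; SE₁ = 0.0554; (0.15 − 0.1143)/0.0554 = 0.645; power 74.0 %.
- Control 50 %, intervention 35 %: SE₀ = 0.0862; SE₁ = 0.0851; (0.15 − 0.1690)/0.0851 = −0.224; power 41.2 %.
- The minimum is 40.5 % at a control rate of about 57.5 %; at 95 % power is 75.0 %.

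The stated range is reproduced and is not in dispute. It concerns the two-arm comparison, not the sub-group analysis.

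**Assumptions for the sub-group check.** The article gives no sick-leave rates by patient factor, so those below are assumed. One binary factor halves each arm: intervention 32/31, control 35/34. Clustering by center is ignored.

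**Within-arm test, no effect and no modification.** With 35 % v 65 % on sick leave in both arms:
- SE₀ = √[0.25(1/32 + 1/31)] = 0.126
- SE₁ = √[0.2275(1/32 + 1/31)] = 0.120
- (0.30 − 1.96 × 0.126)/0.120 = 0.44, so significance is expected in about 67 % of trials.

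Simulation gives 66 %. For weaker or stronger prognosis, the simulated figures are 34 % (40 % v 60 %) and 90 % (30 % v 70 %).

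**Against the interaction test.** This is a Wald test of the difference between the two risk differences, in 20,000 simulated trials per row. Rates are on sick leave, lower/higher factor level.

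| Control | Intervention | Effects by level | Within-arm significant | Interaction significant |
|---|---|---|---|---|
| 35/65 % | 35/65 % | 0 and 0 | 66 % | 5.4 % |
| 35/65 % | 20/50 % | −15 and −15 points | 73 % | 5.7 % |
| 35/65 % | 35/35 % | 0 and −30 points | 5.4 % | 45 % |
| 50/50 % | 50/20 % | 0 and −30 points | 72 % | 45 % |
| 50/50 % | 50/35 % | 0 and −15 points | 22 % | 15 % |

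Rows 1 and 2 have no modification, yet the within-arm test is usually significant. Row 3 has a large modification that it misses. In rows 4 and 5 it does respond to modification, but only because the factor has no prognostic value under usual care, which cannot be known without the controls.

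**Sample size is not the cause.** Double the intervention arm to 64/62, with the rates of row 1: SE₀ = 0.0891, SE₁ = 0.0850, (0.30 − 0.1746)/0.0850 = 1.475, giving about 93 %. More patients make the prognostic signal more significant.

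**Precision of the valid analysis.** SE of the interaction = √[0.25(1/32 + 1/31 + 1/35 + 1/34)] = √(0.25 × 0.1215) = 0.174. The 95 % half-width is 1.96 × 0.174 = 0.34, or ±34 points before clustering.

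**The case against.** The strongest defence is that the sentence describing the analysis speaks of how factors affect RTW and uses the word explore. Alone, it can be read as a plan to study predictors, for which one arm is enough. This stands in part. A reader might infer that the trial will report prognostic factors as differing intervention effects, but the article nowhere says so. What it does is state a purpose of effect modification and attach to it an analysis that cannot serve that purpose.

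A reader might also infer that, with a main comparison of limited power, sub-group statements will carry the published message or decide who is offered the procedure. No text supports that. The primary analysis is a two-arm intention-to-treat comparison, and the Discussion places the study's strength in its organizational data.

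Nor is within-arm analysis wrong throughout. Adherence exists only in the intervention arm, and employer readiness is described only as collected there. Whether the mechanisms were triggered is an implementation question for which description within the arm is suitable.

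The Background supports the prognostic argument directly for only one of the six named factors, symptom severity. The simulated percentages depend on assumed rates; they are the power to detect a real prognostic association, and become errors only if that association is read as modification.

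Finally, the interaction test is weak here: about 15 % power for 0 v −15 points in the example above. That is true, and it means the main gain is correct labelling rather than a firm answer. An analysis plan that is not shown may add detail, but the one-arm restriction is stated in the article and is not an omission.

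**Conclusion.** The point holds for patient factors. The stated purpose (does the effect depend on the patient?) and the stated analysis (sub-groups of the 63 intervention patients) do not match, and no sample size would make them match. Under an assumed 35 % v 65 % split with no effect and no modification, the within-arm comparison is significant in about 66 % of trials (34 % to 90 % over the splits tried), against about 5 % for the interaction test. These figures rest on assumed rates, an even split and no clustering; the logical point rests on none of them.

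The conclusion goes no further than that. It does not show that the investigators will misreport, it does not touch the primary comparison, and it does not reach adherence, employer readiness or the rehabilitation process.

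**What to change.** In Outcome measurements and statistical analyses, separate the two uses.

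1. **Does the effect differ by patient factor?** Analyse a factor-by-arm interaction across both arms, with the same register outcome and model as the main comparison and allowing for center. Limit it to a few pre-named baseline factors available in both arms: for example age and gender, plus baseline symptom severity if control patients completed the baseline questionnaire. Report estimates with confidence intervals, labelled exploratory. Do not use six- and 12-month answers as effect modifiers, since the intervention may itself have changed them.
2. **Adherence, employer readiness, the rehabilitation process and any factor known only in the intervention arm.** Keep the within-arm analysis, but report it as description or as prediction of RTW, not as evidence that the effect differs.

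In the Discussion, add the missing control contrast to small sample size as a limitation of the within-arm results.

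The cost is wording and a few model terms, plus a check of which baseline factors are held for controls, which the article does not state. If controls have no baseline questionnaire, effect modification by severity or motivation cannot be examined and the text should say so. With intervals of about ±34 points before clustering, most sub-group statements will be visibly inconclusive.
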